### Proposed sample size

Assuming the proportion of patients who experience recurrence following RBL is 30% and following HAL is 15%, the sample size required to detect a difference in recurrence rates with 80% power and 5% significance is 121 individuals per group. In order to account for any between-surgeon variation and loss to follow-up, we propose increasing this to 175 per group. This increase is based on the conservative assumption that there will be 14 surgeons in the trial (one per centre) and intra-class correlation (ICC) of 2.5% in keeping with typical ICCs observed by Ukoumunne
[21]. A more likely scenario is that each site will have a minimum of two surgeons, in which case the power to detect this difference is 85%; if there is no between-surgeon variation, the power will be 90%. Because the surgical procedure is well-developed and standardised, intra-class correlation should be virtually zero and the proposed sample size should have closer to 90% power.

The impact of loss to follow up will be minimal for the primary endpoint (haemorrhoidal recurrence at 12 months). Patients who do not complete their 12-month follow-up will have their hospital notes reviewed and their GP will be written to in order to ascertain whether any complications or operative procedures were recorded. The only drop-out expected would be where the patient dies, moves out of the area, or has no traceable patient notes, and we anticipate this would be less than the 5% we have now allowed for in this patient population (a previous study of RBL which used only clinical follow up, reported a 1-year loss to follow up of 10%
[22]).

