### Objectives

The primary research question is does haemorrhoidal artery ligation have a lower recurrence rate than rubber band ligation when used to treat second and third degree haemorrhoids?

The secondary research questions are which of the two procedures is more cost-effective; which is least painful; which has fewest complications and which has the greatest effect on the patients’ quality of life?

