### Outcomes

The primary outcome measure is ‘recurrence’, defined as the proportion of patients with recurrent haemorrhoids at 12 months, as derived from a telephone assessment in combination with GP and hospital records.

The trial is a pragmatic design with a dichotomous outcome. As no validated symptom score exists, we have based our definition of recurrence on Shanmugam et al.’s systematic review
[6] definition:

1. Cured or improved: Symptom free or mild residual symptoms but not requiring further treatment at the end of study period; or,

2. Unchanged or worse: No symptom improvement and requiring further intervention or suffered complication or deterioration of symptoms.”

This study will simplify Shanmugam's criteria into the following question, asked at 12 months by a research nurse:

‘At the moment, do you feel your symptoms from your haemorrhoids are:

1. Cured or improved compared with before starting treatment; or,

2. Unchanged or worse compared with before starting treatment?’

Any patient who answers ‘1’ but has required further treatment since the initial procedure will be reclassified as ‘2’, identified via hospital records, their consultant, their GP and patient questioning.

Secondary outcome measures:

1. Symptom score (adapted from Nystrom et al.
[23])

2. Health related quality of life (using the EuroQol-5D “The EuroQoL group”
[24])

3. Continence questionnaire (using the validated Vaizey Incontinence Score
[25])

4. Pain score (using a 10 cm visual analogue scale)

5. Surgical complications

6. Need for further treatment including details

7. Clinical appearance of haemorrhoids at proctoscopy following recurrence

8. Health care costs

9. Cost effectiveness

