Eligible patients who have given written informed consent to participate in the study will undergo baseline assessment immediately before randomisation (Symptom score, EQ-5D, Continence questionnaire). After their procedure, patients will be asked to complete questionnaires one, seven and twenty-one days after surgery (EQ-5D, Pain score). At six weeks, further data will be collected at the routine follow-up clinic visits (Symptom score, EQ-5D, Pain score, Health and social care resource use questionnaire, Complications review interview, Need for further treatment questionnaire). Finally, one year after their procedure, they will be sent questionnaires (Symptom score, EQ-5D, Continence questionnaire, Health and social care resource use questionnaire, Complications review interview, Need for further treatment questionnaire, Recurrence) and be followed up by telephone. We will measure recurrence (the primary outcome) at 12 months.

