[2]. The former study recommended larger trials and longer follow up. Since it is likely that both surgical complications and recurrence rates will differ at 12 months we will also use decision modelling to extrapolate beyond the trial outcomes. We will draw on and develop as appropriate the model reported in the HTA report
[2]. This model is also being considered for adaptation alongside a model that includes RBL, by those conducting the eTHoS trial (HTA 08/24/02) of stapled haemorrhoidopexy (SH) vs. traditional haemorrhoidectomy (OH). We will liaise with the eTHoS project team to ensure consistency, where appropriate, in our approaches to model adaptation. This will include issues around both model structure and time horizon, as well as parameter values where these are common to both decision problems. This will also avoid unnecessary duplication of workload, particularly in relation to reviewing.

Patients will be asked to complete the EQ-5D instrument at baseline and 1 day, 7 days, 21 days, 6 weeks and 12 months following the treatment. The UK population tariffs will then be used to calculate QALYs for each patient. EQ-5D has been applied in previous studies in this area
[26] and appears to be sensitive to changes in patient outcomes. Pain is likely to be one of the main symptoms in which we might expect the treatments to differ and this is well reflected in the EQ-5D instrument.

In addition, we will explore the relationship between EQ-5D values and specific complications and symptoms, such as relapse, incontinence and pain. We will also consider the relationship between EQ-5D and the combined symptom severity score. These explorations may prove valuable to future modelling studies in this area as there is evidence that previous studies have been hampered by limited utility data. Indeed, a specific recommendation of a recent HTA study was “that further research should include RCTs which collect a generic HRQoL measure such as the EQ-5D or SF-36 at follow-up times close to the procedure and, in the long term, calculate an estimate of preference-based utility. Baseline data from a trial of this kind would also provide a better estimate of HRQoL and utility of patients with symptoms.” (p.88 HTA report
[2])

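### The 12-month recurrence outcome pools never-improved with relapsed patients and is asked once, so the time-to-recurrence analysis and the extrapolation can separate the two only approximately

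*Protocol article*

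**What the plan says.** All references are to the Protocol article.

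- **Objectives.** The primary question is "does haemorrhoidal artery ligation have a lower recurrence rate than rubber band ligation".
- **Outcomes, definition.** A research nurse asks one two-option question at 12 months. The option that scores as an event is "Unchanged or worse compared with before starting treatment". A patient who reports cure or improvement but has had further treatment since the first procedure is also scored as an event.
- **Outcomes, assessment schedule.** "We will measure recurrence (the primary outcome) at 12 months". The six-week visit takes a symptom score, EQ-5D, pain, resource use, complications and a further-treatment form, but not the two-option question. The symptom score is also taken at baseline and at one year.
- **Methods/design.** The six-week visit may fall anywhere from four to twelve weeks after the procedure.
- **Statistical and Health Economic analyses.** Time to recurrence is to be analysed with a Cox model. The main economic analysis is cost per QALY within the 12-month follow-up. Because complications and recurrence are expected to differ at 12 months, "we will also use decision modelling to extrapolate beyond the trial outcomes". An existing model is to be adapted; its structure, horizon and shared parameters are still to be agreed. EQ-5D is also to be related to relapse, among other states.

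**The concern.** Non-response and relapse behave differently over time. Non-response happens once, soon after the procedure. Relapse can continue for as long as responders remain at risk. A 12-month proportion that adds the two is a valid primary outcome, but it is not a rate that can be carried past 12 months.

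The protocol itself shows that early failure is expected. The third recruitment group in Methods/design consists of patients still symptomatic at a follow-up, usually six weeks after a first banding. Under Participants this is called a failure of RBL, whereas the economic section calls the corresponding subgroup recurrence. The Background adds that repeat banding after RBL is common, so the timing of failure may differ between the arms.

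At stake are the two analyses that depend on timing:

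- **Cox model.** It needs event dates. Retreated patients can be dated from records. An untreated patient who answers unchanged at 12 months has no event date from that question.
- **Decision model.** It needs to know how much of each arm's 12-month proportion is finished and how much is still accruing.

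**Working it through.** **Inputs.** From Proposed sample size: 12-month recurrence p = 0.30 (RBL) and 0.15 (HAL). From the economic section: 3 years, the horizon of a cited modelling study of two other operations, used here only for illustration. Assumed, because the protocol gives no figure: the part e of p that is non-response by week 6, and a constant hazard afterwards.

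**The plan's own figure.** The protocol states that the sample size required "with 80% power and 5% significance is 121 individuals per group". Two-sided, without continuity correction, mean proportion 0.225:

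n = [1.960·√(2·0.225·0.775) + 0.842·√(0.30·0.70 + 0.15·0.85)]² / 0.15² = (1.157 + 0.489)² / 0.0225 ≈ 120.5, that is 121. The figure reproduces, so 30% and 15% are a sound starting point. The protocol gives no figure for the extrapolation.

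**All events treated as ongoing relapse, 3 years.**
RBL: 1 − 0.70³ = 65.7%. HAL: 1 − 0.85³ = 38.6%. Gap 27.1 points.

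**Early failure separated.** Cumulative failure at 3 years is

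F = 1 − (1 − e)·[(1 − p)/(1 − e)]^k, with k = (3 − 6/52)/(1 − 6/52) = 3.261.

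Example, RBL with e = 0.20: (0.70/0.80)^3.261 = 0.647; 0.80 × 0.647 = 0.518; F = 48.2%.

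| Early failure e (RBL / HAL) | RBL at 3 years | HAL at 3 years | Gap (points) |
|---|---|---|---|
| None separated | 65.7% | 38.6% | 27.1 |
| 0.15 / 0.075 (half in each arm) | 54.9% | 29.8% | 25.1 |
| 0.20 / 0.02 | 48.2% | 38.4% | 9.9 |
| 0.05 / 0.10 | 64.9% | 25.3% | 39.6 |

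Every row has the same 12-month result, 30% v 15%.

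**Check with a second model.** Non-response is fixed at time zero as a share f of p. The rest is a constant yearly risk r = (p − pf)/(1 − pf) among responders, so F = pf + (1 − pf)·[1 − (1 − r)³].

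| Share f (RBL / HAL) | RBL at 3 years | HAL at 3 years | Gap (points) |
|---|---|---|---|
| 0.5 / 0.5 | 52.5% | 28.2% | 24.3 |
| 1 / 1 | 30.0% | 15.0% | 15.0 |
| 0.75 / 0.25 | 42.9% | 33.7% | 9.2 |
| 0.25 / 0.75 | 59.9% | 22.0% | 37.9 |
| 1 / 0 | 30.0% | 38.6% | −8.6 |

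The two models agree closely. When the early share is the same in both arms, the gap lies between 27 and 15 points. It moves far only when the shares differ strongly, and it changes sign only in the extreme case where every RBL event is early and no HAL event is.

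**The case against.** A reader might infer that the protocol projects early failure forward as continuing relapse. It does not say so. It neither makes the 12-month composite a transition parameter nor assumes a constant rate, and it leaves structure, horizon and parameters open. Model inputs of that kind belong in a fuller document, and their absence from an article is no fault.

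A reader might also infer that the trial cannot tell early from late failure at all. That is too strong. The symptom score at baseline, six weeks and one year, the further-treatment forms, and hospital and GP records all carry timing information.

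Third, a reader might infer that the long-term conclusion could be reversed. All four scenarios in the first table favour HAL, and reversal needs the extreme case in the second. No effect on cost or QALYs has been calculated, and the documents give no basis for strongly unequal early shares. The planned acceptability curve and further sensitivity analyses would cover some of the uncertainty.

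These objections limit the point but do not remove it. By the protocol's own account there is no validated symptom score, and no mapping from the score to the two-option outcome is given. Records date only retreated patients. An acceptability curve reflects uncertainty in the parameters, not whether failure and relapse are separate states in the model. Above all, model inputs can be settled later, whereas a question not asked at six weeks cannot be recovered. The outcome definition and the schedule are things this article does fix.

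**Conclusion.** The point holds as a limit of the outcome and its schedule. Recurrence at 12 months pools non-response with relapse, and asking once means that neither the Cox analysis nor the extrapolation can separate them on the outcome's own scale. Existing data allow an approximate split.

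If the composite were carried forward as a relapse rate, the 3-year gap would be put at 27 points. The same data are compatible with about 25 if half the events are early in both arms, and with about 10 to 40 under strongly unequal shares. These figures rest on assumed shares, an assumed 3-year horizon and a constant later hazard. They show that the difference could be materially misstated, not that it will be, and they do not support a claim of opposite conclusions. The primary comparison and the within-trial cost-per-QALY analysis stand as planned. This is a worthwhile, inexpensive improvement.

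**What to change.** 1. Ask the same two-option question at the existing six-week visit and record the actual date, since the visit may fall at four to twelve weeks. Keep the 12-month outcome as primary.
2. Report by arm: never improved, improved then relapsed, and sustained improvement. Give patients not improved at the early visit but improved at 12 months without further treatment their own line, so that the table is complete.
3. For time to recurrence, use the early answer to place an untreated patient's event before the visit or between it and 12 months.
4. In the decision model, enter non-response as a one-off probability and relapse among early responders as the ongoing rate.

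The cost is one question at a visit that already takes a symptom score and a further-treatment form; no extra patients or visits are needed. The downside is precision. At the planned 175 per group, 15% is about 26 HAL events and 30% about 52 RBL events, and each part of the split is smaller still. The variable visit window also blurs the boundary between failure and early relapse, which is why the date should be kept.

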### Ethical approval

This research has been approved by South Yorkshire REC.

## Discussion

Alongside the eTHoS trial (HTA 08/24/02) the findings of the research will help inform future practice for the treatment of grade II and III haemorrhoids. The results will enable clinicians to provide patients with up-to-date, robust information so that they can make an informed choice of the treatment option most appropriate to their individual needs. Our findings will be disseminated through the Association of Coloproctology of Great Britain and Ireland.

## Abbreviations

AE: Adverse event; CRF: Case report form; CTRU: Clinical trials research unit; DMEC: Data monitoring and ethics committee; GCP: Good clinical practice; GP: General practitioner; HAL: Haemorrhoidal artery ligation; HRQoL: Health related quality of life; NICE: National Institute for Health and Clinical Excellence; NHS: National health service; OH: Open haemorrhoidectomy; QALY: Quality adjusted life year; RBL: Rubber band ligation; RCT: Randomised control trial; SAE: Serious adverse event; ScHARR: School of health and related research; SH: Stapled haemorrhoidopexy; SOP: Standard operating procedure; SOPC: Surgical outpatient clinic; TSC: Trial Steering Committee; VAS: Visual analogue scale.
